#### Sensitivity Analysis

Intermountain Healthcare gathers a vast range of attributes. A different hospital may gather a portion of these attributes. To ensure that the model is generalizable, we will examine miscellaneous attribute combinations and estimate the outcomes of bronchiolitis when using the modified model. Our estimate will determine which attributes are important to include. In the case that an important attribute is nonexistent in a given ED, the estimate can advise substitute attributes that have a minor impact on bronchiolitis outcomes.

Our complete model will include as many as 400 attributes. Conducting simulations for each possible combination of the attributes is not realistic because of the exponential growth of the number of combinations. As an alternative, an attribute grouping approach will be used. This approach associates attributes that commonly coexist based upon the judgment of our clinical experts. If an attribute in a group is not recorded by a hospital, related attributes in the group are also likely to be missing, such as attributes from the same lab test panel. Grouping will allow us to create and publish a table that lists the groups of possible attribute combinations, including bronchiolitis outcomes estimated via simulations and the trained parameters of the predictive model. If a hospital shows interest in implementing the model, the table can help assess expected outcomes in their environment, whether additional attributes need to be gathered, and if so, which ones. One row in the table will reflect the attributes in the PHIS+ [64] data model that standardizes administrative and clinical attributes from 6 major US children’s hospitals. The model of the row will apply directly to at least these 6 hospitals.

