## Methods

Machine learning is a field that studies the automatic improvement of computer algorithms with experience. Machine learning methods—such as support vector machine, neural network, and decision tree—are commonly used in predictive modeling [36] and will be adopted in our study. In comparison to statistical methods, machine learning can improve prediction accuracy, occasionally doubling it, with less stringent assumptions on data distribution [38,42,43].

For all 3 aims, we will use the same patient population and data sets:

Patient population: Our study cohort includes children under age 2 who had ED encounters at 22 Intermountain Healthcare facilities for bronchiolitis (ICD-9-CM discharge diagnosis code 466.1 [4]) in the past 10 years. Intermountain Healthcare is the biggest health care system in Utah, comprising 185 clinics and 22 hospitals.Data sets: A large administrative and clinical data set in the enterprise data warehouse (EDW) of Intermountain Healthcare will be used. The Intermountain Healthcare EDW contains a vast set of attributes [44]. Our Intermountain Healthcare data analyst will run SQL queries to obtain a data set that has been de-identified and encrypted and then securely transfer it to a computer that is encrypted and password-protected. Secondary analysis will be conducted on the computer. Intermountain Healthcare has dedicated tables to identify changes in procedure and diagnosis codes. The data set contains electronic documentation of about 85% of pediatric care delivered in Utah [45] and includes approximately 400 attributes. A partial list of categories of these attributes includes: admission date and time; age; orders (eg, medications, labs, exams, immunizations, imaging, counseling, etc), including order name, ordering provider, performing date, and result date; allergies; chief complaint; diagnoses; discharge date; exam result; facility seen for the patient visit; gender; health insurance; health care cost (billed charge, Intermountain Healthcare internal cost and reimbursed cost); height; home address; immunizations; lab test result; language(s) spoken; medication refills; primary care physician as listed in the electronic medical record; problem list; procedure date; procedures; provider involved in the visit; race/ethnicity; referrals; religion; visit type (inpatient, outpatient, urgent care, or emergency department); vital signs; and weight [46].

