#### Sample Size Justification and Performance Evaluation

We have 10 years of data. We will train and test predictive models using a standard method. We will perform stratified 10-fold cross validation [56] on the initial 9 years of data to train predictive models and provide estimates of their accuracy. Data from the tenth year will be used to evaluate performance of the best-performing machine learning algorithm, reflecting use in practice. To figure out the environmental variable, administrative, and clinical attributes necessary for high accuracy, we will use backward elimination [36] to remove input variables so long as the AUROC does not decrease by more than 0.02 or go below 0.9.

No AUROC achieved by current care has been reported before. By extrapolating from statistics reported in the literature (unnecessary admissions up to 29% and unsafe ED discharges of 6%), we anticipate the AUROC achieved by current care to be between 0.6 and 0.8+ [20-24,27]. We will test the hypothesis that the model’s prediction will be more accurate by a difference in AUROC of larger than or equal to 0.05. The dependent variable has 2 possible values: appropriate hospital admission and appropriate ED discharge. Assuming a correlation coefficient of 0.6 between the model’s prediction result and the actual disposition decision for both values and using a 1-sided Z-test at a 0.05 significance level, a sample size of 356 instances per possible value of the dependent variable will have 90% power to detect an AUROC increase of 0.05. Data from the tenth year include 3615 ED visits for bronchiolitis, which provides adequate power for testing our hypothesis.

Based on 2 prior studies’ results, we anticipate that our model will achieve an AUROC larger than or equal to 0.9 and outperform current care in making disposition decisions. Neither prior study on predicting a bronchiolitis patient’s ED disposition is similar to our study, which uses appropriate admission as the gold standard. The first study [21] used actual admission as the gold standard and achieved an AUROC of 0.87. The second study [34] used judgment of an attending pediatrician as well as a length of stay longer than 1 day as the gold standard. The predictive model achieved 81% accuracy, better than an average admitting resident’s disposition decision.

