### Aim 3: Conduct Simulations to Estimate the Impact of Using the Model on Bronchiolitis Outcomes

We will use a method similar to that in Luo et al [46] to establish the model’s utility for future use in clinical practice. More specifically, we will estimate the impact of using the model on bronchiolitis outcomes by applying the model to a retrospective cohort, and determine how the model can be generalized to different sites that collect differing sets of attributes. Our model will be developed using data from Intermountain Healthcare. Our simulations will help determine how to implement the model in other EDs. No prior study has either assessed the impact of using a predictive model on bronchiolitis outcomes or found the set of attributes most essential to generalize the model.

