## Discussion

The principle of our approach to developing an operational definition of appropriate hospital admission in the ED is general and can be used for other diseases beyond bronchiolitis. Our simulation method will ascertain how a predictive model can be generalized to different sites collecting various sets of attributes, as well as the group of attributes most essential for generalization. This study will use data from a big health care system with numerous heterogeneous facilities spread across a large area. These facilities include EDs at 22 hospitals, ranging from community metropolitan and rural hospitals attended by general practitioners and family doctors with constrained pediatric resources to tertiary care children’s and general hospitals in urban areas attended by subspecialists. Each of these facilities has a differing patient population, scope of services, geographic location, staff composition, and cultural background. This variation creates a realistic situation for identifying factors that are generalizable to other facilities across the United States. One of the models produced during simulation will directly apply to at least 6 large US children’s hospitals. Moreover, this study will produce a new modeling strategy that can be generalized to other clinical conditions where decision making is uncertain.

In summary, our work will transform bronchiolitis care by developing a new predictive model to guide appropriate admission for ED patients with bronchiolitis. Broad use of the model will lower health care use and cost and improve clinical outcomes for bronchiolitis patients. We will have a new simulation method to estimate the impact of using a predictive model on outcomes in dissimilar data environments. The method can be useful for implementing other models.

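### The article says one model will apply directly to at least 6 children's hospitals, but the planned analyses test attribute availability within one health system, not performance at a hospital that supplied no training data

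*Protocol article*

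**What the plan says.** **Data.** Methods states: "For all 3 aims, we will use the same patient population and data sets". The cohort comes from 22 facilities of one health system, and the introduction to Aim 3 confirms: "Our model will be developed using data from Intermountain Healthcare". The facility visited is a recorded attribute.

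**Validation.** Aim 2 uses stratified 10-fold cross-validation on the first 9 years, and then: "Data from the tenth year will be used to evaluate performance of the best-performing machine learning algorithm, reflecting use in practice". Aim 3 (Estimate a Model's Impact) reuses the same division by year.

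**Generalizability.** Aim 3, Sensitivity Analysis, names one step: "To ensure that the model is generalizable, we will examine miscellaneous attribute combinations". The results go into a published table of attribute combinations, simulated outcomes and trained model parameters. For a hospital thinking of adopting the model, "the table can help assess expected outcomes in their environment".

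**The 6 hospitals.** The same section says: "One row in the table will reflect the attributes in the PHIS+ [64] data model", and then: "The model of the row will apply directly to at least these 6 hospitals". The Discussion repeats the statement without a condition: "One of the models produced during simulation will directly apply to at least 6 large US" children's hospitals.

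**The concern.** Having the same input columns is necessary for using a model at another hospital, but it does not show that the model will perform there as it did where it was built. Case mix, admission practice, coding, measurement and cost can all differ, and the article itself stresses practice variation and variable admission rates.

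Three features of the plan tie its results to this system:

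- The outcome label is set from local data. The return threshold is a 95th percentile and the intervention threshold a median, both taken from this cohort (Aim 1).
- The primary outcome of Aim 3 is the system's own internal cost.
- The Discussion cites the differences among the 22 facilities as support for generalizing, but no analysis by facility is planned.

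An adopting hospital could therefore read the simulated admissions, ED returns and costs in its row as a forecast for itself. Those figures would include no between-hospital uncertainty.

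**Working it through.** No stated figure is in dispute, so there is none to reproduce. The check has two parts.

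**1. What each planned step can show**

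| Step | Held out | What it tests |
|---|---|---|
| 10-fold cross-validation, years 1-9 (Aim 2) | Random folds | Fit to similar visits in the same system |
| Year-10 test (Aims 2 and 3) | A later year | Stability over time in the same system |
| Attribute combinations (Aim 3) | Input groups, same division by year | Effect of missing inputs |
| Direct application to 6 hospitals; expected outcomes elsewhere | Would need unseen hospitals | Not tested by any step |

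The first three rows are sound for their own purposes. None supplies evidence for the fourth.

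**2. Whether a hospital hold-out is workable with the data in hand**

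Inputs from the article:

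- 26,701 patients (Innovations), 22 facilities (Methods), 3615 visits in year 10 (Aim 3).
- Target AUROC of 0.9 (Aim 2).
- 32%-40% admitted, 20%-29% of admissions unnecessary, 6% of discharges unsafe (Introduction).

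Assumptions: equal volume per hospital, because the article gives no volumes by site, and one visit per patient.

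Share of appropriate admissions (necessary admissions plus unsafe discharges):

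- Low: 0.32 × 0.71 + 0.68 × 0.06 = 0.268
- High: 0.40 × 0.80 + 0.60 × 0.06 = 0.356

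Mean volume per hospital:

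- All years: 26,701 / 22 ≈ 1,214 patients
- Year 10 only: 3615 / 22 ≈ 164 visits

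Hanley-McNeil standard error, with Q₁ = A/(2 − A) and Q₂ = 2A²/(1 + A):

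SE = √{[A(1 − A) + (n₁ − 1)(Q₁ − A²) + (n₀ − 1)(Q₂ − A²)] / (n₁n₀)}

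For A = 0.90 and 1,214 patients with a mid-range share of 30% (n₁ = 364, n₀ = 850): Q₁ = 0.8182 and Q₂ = 0.8526. The numerator is 0.09 + 363 × 0.00818 + 849 × 0.04263 = 39.25. Then 39.25 / 309,400 = 0.000127, and SE = 0.0113.

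Over the range of shares (rounded to 0.27 and 0.36):

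| Held-out hospital | SE | 95% half-width |
|---|---|---|
| 1,214 patients (all years) | 0.010-0.012 | 0.020-0.023 |
| 164 visits (year 10 only) | 0.028-0.032 | 0.056-0.063 |
| 50 visits (assumed small site) | 0.052-0.059 | 0.10-0.12 |

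If the hold-out is confined to years 1-9, at least 26,701 − 3615 = 23,086 patients remain, taking the 26,701 to span all ten years. That is about 1,049 per hospital, with an SE of 0.011-0.013, so the conclusion is unchanged. Several pooled years are informative at an average or large hospital. Year 10 alone is weak, and small hospitals need pooling.

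**The case against.** **The aim is narrow.** The introduction to Aim 3 limits generalization to sites that collect different sets of attributes, and Innovations describes the problem as attributes missing from other record systems. A reader might infer that the stated aim goes unanswered. That is not supported: varying the attributes does address this aim. What goes further is the claim of direct application and the offer of expected outcomes elsewhere.

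**Direct application may mean only that the inputs exist there.** The sentence follows straight after the description of the shared data model, so this reading is fair. But the article does not limit the phrase, and the same paragraph offers the table for judging outcomes in another hospital's environment. That offer is hedged, but it concerns performance.

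**The remedy does not test the 6 hospitals.** This stands. Leave-one-hospital-out stays within one health system, so the wording must change whether or not the validation is added. The article also does not say whether any of the 6 belongs to this system; that they are outside is an inference, though the section's reference to a different hospital supports it.

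**Equal volume is implausible.** This stands too. The Discussion describes sites from rural community hospitals to tertiary children's hospitals.

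**A randomized trial is planned later.** It is a separate study and is not described as taking place at these hospitals.

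**Conclusion.** The point holds as a mismatch between claim and evidence. The plan supports a statement about which attributes are needed and what is lost without them. It does not support an unconditional statement that a model will apply directly to 6 hospitals, or reading the table as a forecast for a hospital that supplied no training data. The main AUROC and cost tests are unaffected.

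The size of any loss at a new site is unknown, because the article gives no between-hospital variation. If the between-hospital SD of AUROC were 0.03-0.05, a new hospital's 95% range around 0.90 would be 0.84-0.96 (0.90 ± 1.96 × 0.03) or 0.80-1.00 (0.90 ± 1.96 × 0.05). This is purely illustrative. A reader might go on to infer that the model would do worse than current care at some hospitals. The article does not support that: the SD is assumed, current care would vary by hospital as well, and the article's own expectation for current care is wide (0.6 to 0.8+). Nor should one infer that the table would report a misleading AUROC, since AUROC is not among its listed contents. The exposure is in the simulated outcomes, cost above all.

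The feasibility figures rest on equal volume, one visit per patient and an AUROC of 0.90.

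**What to change.** 1. **Narrow the wording.** In Aim 3, Sensitivity Analysis, and in the Discussion, replace the statement of direct application with *uses only attributes available at* the 6 hospitals. State beside the table that its outcome estimates reflect this health system and its internal costs, pending external validation.

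2. **Add leave-one-hospital-out validation within years 1-9**, for at least the complete model and the PHIS+ row. Exclude facility identity as a predictor and pool small hospitals. Report AUROC and simulated cost by hospital, with a random-effects summary and a prediction interval. Present this as evidence of variation between sites in this system, not as validation for the 6 hospitals. Year 10 stays as the planned test.

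**Cost.** The wording change costs nothing beyond a less favourable generalizability statement. The validation needs no new data, since facility is recorded, and extraction is still under way, so it can be specified before results. It takes up to 22 refits for each of the two models (fewer after pooling). That is a real addition, because hyper-parameters are tuned by hand and the cluster is planned only if one computer proves too slow. Intervals at small sites will be wide.

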#### Sample Size Justification and Performance Evaluation

We will test 3 hypotheses: use of our predictive model will be linked to reduced (1) costs, (2) ED returns, and (3) hospital admissions. Due to their skewed distribution, cost data will be log-transformed [52]. The primary hypothesis will be accepted if the model lowers the log cost by at least 10% of its standard deviation. We will use 1-sided paired-sample t-test to assess the log cost difference between the model’s prediction result and the actual disposition decision. We will use McNemar’s test to assess the difference in ED returns and hospital admissions. A sample size of 857 data instances has 90% power to support the primary hypothesis at a 0.05 significance level. Data from the tenth year include 3615 ED visits for bronchiolitis, which offers sufficient power for testing the primary hypothesis.

If performing simulations on 1 computer is too slow for the numerous combinations of attribute groups, we will conduct parallel simulations on the secure Homer computer cluster [60].

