#### Outcomes

We will assess the outcomes of hospital admission, discharge to home, cost, and ED return. The primary outcome is cost. Other outcomes are indirectly reflected in cost and secondary. Each medical claim is companioned by a billed cost, a reimbursed cost, and an Intermountain Healthcare internal cost [52]. The Intermountain Healthcare internal cost [62] will be used because it is subject to less variation resulting from member cost-sharing [52] and more closely reflects actual cost. To deal with inflation, the medical consumer price index [63] will be used to standardize costs to 2014 US dollars. ED returns will be computed using the time interval defining unsafe discharge.

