#### Estimate a Model’s Impact

Given a predictive model and a set of input variables, we will estimate the impact of using the model on each outcome. The same method in Aim 2 will be used to train the model on data from the first 9 years. Data from the tenth year have 4 groups: (1) necessary admissions, (2) unnecessary admissions, (3) unsafe discharges, and (4) safe discharges (Figure 1). For each group, we will obtain prediction results, then estimate the outcome if the model’s suggestions were followed. For example, consider necessary admissions. The model will erroneously predict that some of these patients should be discharged. We assume that in clinical application, every such patient will incur an unsafe discharge, an early return visit for bronchiolitis, and a cost equal to unsafe discharges’ average cost. The overall estimated outcome is the aggregate of outcome estimates in all 4 groups. Similarly, we can determine the minimum requirement of the model’s accuracy for the model to be valuable clinically.

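### Aim 3 gives redirected visits a group's average cost but tests the primary hypothesis on log cost, which understates savings if that average is arithmetic and compares geometric means rather than mean cost

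*Protocol article*

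**What the plan says.** All of this is in the Aim 3 part of the protocol article.

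- **Outcomes:** "The primary outcome is cost", measured as the health system's internal cost in 2014 US dollars.
- **Estimate a Model's Impact:** tenth-year visits fall into four groups (necessary admissions, unnecessary admissions, unsafe discharges, safe discharges). The worked example is a necessary admission that the model would send home. Such a visit is given "a cost equal to unsafe discharges’ average cost". Then "The overall estimated outcome is the aggregate of outcome estimates in all 4 groups".
- **Sample Size Justification and Performance Evaluation:** the hypotheses are that "use of our predictive model will be linked to reduced (1) costs, (2) ED returns, and (3) hospital admissions". The scale and test follow: "Due to their skewed distribution, cost data will be log-transformed", and "We will use 1-sided paired-sample t-test to assess the log cost difference between the model’s prediction result and the actual disposition decision". Success requires a fall in log cost of at least 10% of its SD. The stated sample size is 857 for 90% power at the 0.05 level, with 3615 visits available.

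No log-scale averaging, retransformation or dollar-scale test is stated.

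**The concern.** Two separate problems come from combining these steps.

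1. **Imputation.** A visit that keeps its disposition keeps its own cost. A redirected visit gets a group average in place of an individual cost. With skewed costs, the log of an arithmetic average is larger than the average of the logs, so redirected visits move up on the log scale even when nothing has changed in dollars. The skewness that motivates the log is also what makes this gap large.
2. **Estimand.** A mean difference in logs is the log of a ratio of geometric means. The hypothesis, and the resource argument in the article's Introduction and Discussion, concern cost, that is, mean or total dollars. The log compresses errors on expensive admissions, so the two measures can disagree in sign.

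At stake is the primary conclusion of Aim 3. Under Sensitivity Analysis, the article also plans to publish outcome estimates for other hospitals to use.

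**Working it through.** **The plan's own figure.** For a one-sided paired test, n = ((z₀.₉₅ + z₀.₉₀)/0.10)² = ((1.645 + 1.282)/0.10)² = 856.4, rounded up to 857. This reproduces; the exact t calculation gives 858. In this formula 0.10 is the mean difference divided by the SD of the paired differences.

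**Inputs from the article.** Admission rate 36% (middle of 32%-40%), 29% of admissions unnecessary, 6% of discharges unsafe. Group shares:
- necessary admission (NA): 0.36 × 0.71 = 0.2556
- unnecessary admission (UA): 0.36 × 0.29 = 0.1044
- unsafe discharge (UD): 0.64 × 0.06 = 0.0384
- safe discharge (SD): 0.64 × 0.94 = 0.6016

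**Assumed, because the article does not give them.** Log-normal costs with a common within-group log SD (σ); group mean costs for NA/UA/UD/SD of $8000/2500/12000/800 (set 1) or $6000/2500/7000/600 (set 2); the model's error rates. Redirection NA→UD is stated. UA→SD, UD→NA and SD→UA are inferred from the example.

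**Formula.** For log-normal cost with mean m, E[ln C] = ln m − σ²/2. A visit moved from group g to the arithmetic mean of group h therefore changes on average by ln(m_h/m_g) + σ²/2. Imputing the mean log cost of h would give ln(m_h/m_g). The excess is σ²/2 per redirected visit: 0.125 at σ = 0.5 and 0.405 at σ = 0.9.

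**Check 1: no true effect.** All groups have the same cost distribution; 10% of NA, 60% of UA, 60% of UD and 10% of SD are redirected (17.1% of visits). Mean dollars do not change. Mean log cost rises by 0.1714 × 0.125 = 0.021 (0.043 SD) at σ = 0.5, and by 0.1714 × 0.5 = 0.086 (0.086 SD) at σ = 1.0. The success margin is 0.10 SD.

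**Check 2: perfect classifier.** All UA and all UD are redirected (14.28% of visits). In set 1, mean cost is $3247.9 and the saving is 0.1044 × 1700 + 0.0384 × 4000 = $331.1, or 10.2%. In set 2 it is $236.8 of $2424.4, or 9.8%. For set 1 at σ = 0.5, the log change is 0.1044 × (−1.139 + 0.125) + 0.0384 × (−0.405 + 0.125) = −0.106 − 0.011 = −0.117. The SD of log cost (within plus between groups) is 1.168, so the fall is 0.0999 SD.

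| Set | σ | Log change | Fall in SD of log cost | Same, imputing mean log cost | Fall in SD of paired differences |
|---|---|---|---|---|---|
| 1 | 0.5 | −0.117 | 0.100 | 0.115 | 0.32 |
| 1 | 0.7 | −0.100 | 0.079 | 0.106 | 0.26 |
| 1 | 0.9 | −0.077 | 0.055 | 0.097 | 0.19 |
| 2 | 0.5 | −0.137 | 0.118 | 0.133 | 0.31 |
| 2 | 0.7 | −0.120 | 0.095 | 0.123 | 0.27 |
| 2 | 0.9 | −0.097 | 0.070 | 0.112 | 0.21 |

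Measured in SD of log cost, four of the six cases fall clearly short of 0.10, one sits on it and one passes. With mean log cost imputed, five of the six pass.

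**Check 3: sign conflict.** Set 1, σ = 0.5; the model sends home 25% of NA, redirects 80% of UA, catches 50% of UD and admits 2% of SD.
- Dollars: 0.0639 × 4000 − 0.0835 × 1700 − 0.0192 × 4000 + 0.0120 × 1700 = +$57.3 per visit, and 57.3/3247.9 = +1.8%.
- Logs: 0.0339 − 0.0847 − 0.0054 + 0.0152 = −0.041.
- The SD of the paired differences is 0.41, so the fall is 0.100 of that SD and t ≈ −0.100 × √3615 ≈ −6. Against the SD of log cost it is 0.041/1.168 = 0.035.

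The opposite conflict also occurs. In set 2 with σ = 1.0, 5% of NA, 60% of UA, 60% of UD and 5% of SD redirected, mean cost falls by about $72 per visit (3.0%) while log cost rises by 0.016. With mean log cost imputed, it would fall by 0.048.

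**The case against.** - **The averaging rule is partly inferred.** It is given for one group, as an example. The article does not say arithmetic, and it does not fix the order of averaging and taking logs. It also says the method resembles that of a cited study, which is not at hand. If the averaging is done on the log scale, the artefact vanishes. This stands as a limit on the first problem, although arithmetic is the ordinary reading. It does not touch the second.
- **The artefact is conservative.** A reader might infer that the imputation could produce a false claim of savings. It cannot: it raises log cost and so works against the model. A falsely favourable result can come only from the geometric-mean problem.
- **A significant test is not yet success.** A reader might infer from Check 3 that the plan would accept a model that raises cost. That follows only if the 10% refers to the SD of paired differences (0.100); against the SD of log cost, 0.035 is far short. Conversely, the perfect classifier fails only if the SD is that of log cost; against paired differences (0.19 to 0.32) it passes easily. The rule's grammar points to log cost and the 857 to paired differences, so the article does not settle which applies.
- **Dollar cost remains visible.** Outcomes are aggregated over the four groups, so a rise in cost could be seen beside the test. That is true, but the acceptance rule rests on log cost alone.
- **Logging skewed costs is recognised practice.** It is, for testing. It does not turn the result into a statement about mean cost, and with 3615 visits skewness does not force the choice.

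**Conclusion.** The concern holds in a limited form. If the group average is arithmetic, redirected visits are shifted up by σ²/2 in log cost on average. Under the assumed costs and σ of 0.5 to 0.9, a perfect classifier saving about 10% of mean cost then shows only 0.055 to 0.118 SD of log cost, below the 0.10 margin in most cases on that reading of SD. Independently of the averaging rule, the primary test concerns geometric means while the hypothesis concerns cost, and the two can differ in sign.

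The direction of the shift follows from the method. Every size above is illustrative, since the article reports no group costs, SDs or error rates. A reader might go further and infer that the primary result will be wrong, or that the 857 is miscalculated. The documents support neither: the 857 is arithmetically correct for its scale, and how far the result is affected depends on data not shown. This is a should-fix point.

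**What to change.** 1. Make the mean cost difference per visit, in dollars, the primary analysis. Use a paired bootstrap that resamples patients and recomputes the group averages in every resample, so that their uncertainty is carried through. Report a one-sided 95% bound.
2. Restate the success margin and the 857 for the dollar scale, and say which SD any SD-based margin refers to.
3. State the averaging rule for all four groups.
4. Keep log cost as a secondary analysis, imputing the mean log cost of the destination group rather than the log of its mean.

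The cost is a change of analysis wording, a bootstrap and a new sample-size statement, with no new data. The drawback is somewhat wider intervals on the dollar scale; 3615 visits are already available.
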